### Interim analyses {21b}

Two interim analyses are planned for the primary outcome of extubation failure: (1) after 50% and (2) 75% of the subjects have completed the primary outcome.

### Methods for additional analyses (e.g., subgroup analyses) {20b}

Prior studies offer no basis for assuming a priori interactions between treatment arms and subgroups defined by sex, race/ethnicity, gestational age, site or a combination of these groups, beyond that already controlled for in the randomization. For that reason, preplanned tests for interactions with treatment assignment are not warranted, and not powered for. We will, however, table all results by subgroups for descriptive purposes and to explore in secondary analyses possible subgroup differences by treatment group, solely for purposes of generating hypotheses for future studies. The subgroups will include sex, race/ethnicity, gestational age, site, maternal corticosteroid use, reason for initial intubation, and days intubated prior to extubation attempt. Efficacy in NAVA naïve versus non-naïve sites will be compared. Subgroup analyses will use either permutation tests or regression models (GEEs) with a subgroup-arm interaction term based on subgroup sample size and distributional properties of the randomization scheme in the subgroup.

For the 36 weeks’ PMA outcomes, evaluating the interaction between the primary outcome, treatment arm, and reintubation rates will be important for future clinical trial design. Subgroup analyses exploring these interactions will be performed for all outcomes evaluated after the primary outcome. For non-mortal 36 weeks’ PMA/discharge secondary outcomes, death many be a censoring event. We will compare the characteristics of the survivors to infants who die using standard descriptive statistics. Rates will be summarized and compared within all infants and within survivors only. Death will be coded as time of censoring in time-to-event outcomes [31].

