### Secondary study endpoints

The DIVA trial is not powered to identify the impact of NIV-NAVA on all later respiratory outcomes. However, exploratory analyses of the impact of NIV-NAVA on respiratory outcomes and the association between timing and occurrence of extubation failure on longer-term respiratory morbidity among extremely preterm infants will be conducted. Enrolled infants will be followed until 36 weeks PMA for the following secondary outcomes:Bronchopulmonary dysplasia at 36 weeks PMA, as defined by Jensen et al. [29]Composite of death/BPDEndotracheal intubation, including time and reason for intubationPMA at last mechanical ventilation, last positive pressure, and last supplemental oxygenPost-randomization postnatal steroidsBrain injury (intraventricular hemorrhage and periventricular leukomalacia)Patent ductus arteriosus requiring therapyPulmonary hemorrhageCulture proven sepsisNecrotizing enterocolitisRetinopathy of prematurityTime to deathAir leaksGastrointestinal perforation or bleeding

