### Sample size {14}

The calculated study sample size accounts for 478 infants in the randomization phase. Very little published data exists for reintubation rates using NIV-NAVA or NS-NIPPV in our study population. In a recent pilot RCT of more mature preterm infants (median 27 weeks’ gestation), 9% of infants managed with NIV-NAVA were reintubated within 5 days [30]. Our preliminary data indicates a higher failure rate in our more immature study population (Table 1). Sample size estimates were based on having 90% power to detect a 15% absolute risk reduction in extubation failure among infants treated with NIV-NAVA, compared with non-synchronized NIPPV, assuming a two-sided test, family-wise error rate of 0.05 and a group sequential design with 2 interim analyses. The interim analyses were set after 50% and 75% of the infants have completed the primary outcome and used Len-DeMets spending functions of the O’Brien-Fleming type. Simulation studies were used to determine that interim analyses prior to 50% completion of the primary outcome were highly unlikely to result in any clinically meaningful differences in the primary efficacy and safety outcomes while reducing power for the final analysis.

Preliminary data from the DIVA trial sites informed sample size calculations: following extubation, 40% of infants treated with NS-NIPPV were reintubated within 5 days, and 19% of infants treated with NIV-NAVA were reintubated within 5 days (Table 1). This reintubation rate for NS-NIPPV is consistent with the reintubation rate of 37% among infants treated with NIPPV in the largest trial of NIPPV vs. CPAP (*n* = 1009) [19].

Thus, we conservatively anticipate a 5-day extubation failure rate of 35% in the NS-NIPPV group. We assume *90% power* and a two-sided proportions test. To detect a 15% absolute reduction in the rate of extubation failure rate in the NIV-NAVA group would require 406 infants. We expect 25% of enrolled infants to be from a multiple birth (based on the PIs’ previous trials and published papers). The multiple birth design effect is 1.15, assuming an intraclass correlation coefficient of 0.6. Inflating the required sample size for the design effect and conservatively allowing for 2% drop-out prior to the primary outcome results in 478 randomized infants (Table 4).

**Table 4 Tab4:** Sample size requirements for the primary outcome

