## Statistical methods

### Statistical methods for primary and secondary outcomes {20a}

The proposed study is a two-arm parallel design of two alternative courses of treatment. A modified “as-randomized” analysis (or “intention-to-treat” analysis) (mITT) will estimate whether NIV-NAVA is superior to NS-NIPPV in avoiding treatment failure and is at least as good as NS-NIPPV in avoiding adverse events.

Among infants randomized before extubation, there is a risk that infants will become ineligible for extubation (and from the trial) after randomization due to changes in clinical status. Therefore, a mITT analysis has been planned. Only infants whose eligibility changes due to new/emergent conditions not known at the time of randomization will be excluded from the primary outcome analysis set in the mITT analysis. This number is expected to be minimal and will be closely monitored. A sensitivity analysis using a conventional ITT analysis will also be conducted.

The primary outcome will compare rates of extubation failure between the treatments using logistic regression. The regression model will be fitted using robust clustered standard errors under the generalized estimating equation (GEE) framework, with an exchangeable correlation structure for clusters based on infant mother, i.e., adjusting for the inherent correlation between infants that are multiples. The primary analysis will include clinical site, gestational age, biological sex, and days of invasive ventilation prior to extubation as fixed effects, to control for any residual confounding and site-level treatment imbalance from the stratification factors. Standard regression diagnostics will be used to assess model adequacy and to examine for potential outlying or influential data points.

Secondary efficacy and safety outcomes will be analyzed using similar procedures to the primary outcome. Comparisons between treatment arms will use GEE based logistic regression (dichotomous outcomes), linear regression (continuous outcomes), Poisson regression (count outcomes), or survival analysis (time based outcomes), as appropriate.

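### 36-week arm contrasts within groups defined by extubation failure or reintubation are not protected by randomisation and can show a false excess of BPD on NIV-NAVA

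*Protocol article*

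**What the plan says.** The second paragraph of the protocol's section on additional analyses {20b} deals with outcomes at 36 weeks' postmenstrual age. It states that "evaluating the interaction between the primary outcome, treatment arm, and reintubation rates will be important for future clinical trial design", and then: "Subgroup analyses exploring these interactions will be performed for all outcomes evaluated after the primary outcome". The primary outcome is extubation failure within 5 days, so the groups in question are formed by failure and by reintubation, with treatment arm as a further term.

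The method is given in the paragraph before, which lists mainly baseline subgroups: "Subgroup analyses will use either permutation tests or regression models (GEEs) with a subgroup-arm interaction term". That paragraph restricts its subgroup results to use "solely for purposes of generating hypotheses for future studies". The restriction is not repeated for the failure and reintubation groups.

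Two other statements set the context. Secondary study endpoints announces "exploratory analyses of the impact of NIV-NAVA on respiratory outcomes and the association between timing and occurrence of extubation failure on longer-term respiratory morbidity". Statistical methods {20a} says: "Secondary efficacy and safety outcomes will be analyzed using similar procedures to the primary outcome". The main 36-week comparisons are therefore made by arm in the modified as-randomised set.

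**The concern.** A subgroup-by-arm analysis is sound when the subgroup is fixed before randomisation, because the arms are then comparable within each level. Failure and reintubation are not fixed before randomisation. The trial is powered on treatment changing the failure rate, so under the design hypothesis the two failure groups contain different infants. The infants who still fail on NIV-NAVA are on average a frailer remainder. Its successes include infants who would have failed on NS-NIPPV.

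The protocol itself supplies the link to BPD. The background {6a} associates repeated courses of ventilation with BPD, and the discussion of the primary outcome definition associates reintubation in the first 48 h with BPD. The rationale for the primary endpoint adds that reintubation could be open to performance bias in an unblinded trial, so reintubation groups might also differ by arm through clinician behaviour.

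The stated use of these analyses is future trial design. A false signal of harm within failure groups could mislead that work.

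**Working it through.** **1. The design rates.** Sample size {14} states "we conservatively anticipate a 5-day extubation failure rate of 35% in the NS-NIPPV group" and "90% power to detect a 15% absolute risk reduction in extubation failure among infants treated with NIV-NAVA", that is, 35% against 20%.
- A two-sided test of proportions at 0.05 with continuity correction gives 396 infants in total.
- Lan-DeMets O'Brien-Fleming looks at 50%, 75% and 100% inflate this by 1.018: 396 × 1.018 = 403, against the stated 406.
- 406 × 1.15 / 0.98 = 476, against the stated 478.

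The plan's figures reproduce closely, so 35% and 20% are a fair basis.

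**2. Group sizes.** 478 × 0.98 / 2 = 234 infants per arm. Failures: 234 × 0.20 = 47 on NIV-NAVA and 234 × 0.35 = 82 on NS-NIPPV. Successes: 187 and 152.

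**3. Bias with no treatment effect on BPD.** Assume 20% of infants fail on either mode, 15% fail only on NS-NIPPV and 65% fail on neither. The BPD risks below are assumptions.

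Gradient 80/60/40%: overall BPD is 0.20×0.80 + 0.15×0.60 + 0.65×0.40 = 51% in both arms.
- Failures: NIV-NAVA 80.0%; NS-NIPPV (0.16 + 0.09)/0.35 = 71.4%; difference +8.6 points.
- Successes: NIV-NAVA (0.09 + 0.26)/0.80 = 43.8%; NS-NIPPV 40.0%; difference +3.8 points.

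Gradient 70/60/50%: overall 55.5% in both arms.
- Failures: 70.0% against (0.14 + 0.09)/0.35 = 65.7%; +4.3 points.
- Successes: (0.09 + 0.325)/0.80 = 51.9% against 50.0%; +1.9 points.

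**4. Some infants fail only on NIV-NAVA.** Keep the 35% and 20% margins and 51% overall, with 10% failing on both modes (BPD 80%), 25% only on NS-NIPPV (60%), 10% only on NIV-NAVA (60%) and 55% on neither (40%).
- Failures: (0.08 + 0.06)/0.20 = 70.0% against (0.08 + 0.15)/0.35 = 65.7%; +4.3 points.
- Successes: (0.15 + 0.22)/0.80 = 46.3% against (0.06 + 0.22)/0.65 = 43.1%; +3.2 points.

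**5. A second model.** One latent severity, bivariate normal, drives both failure and BPD. The arm has no effect on BPD, and overall BPD is assumed at 30% to 60%. False excess on NIV-NAVA, and the chance of nominal significance at two-sided 0.05 in one group, unadjusted and with infants treated as independent:

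| Latent correlation | Among failures (points) | Among successes (points) | Chance of p < 0.05 |
|---|---|---|---|
| 0 | 0 | 0 | 5% |
| 0.2 | +2.5 to +2.7 | +1.5 to +1.8 | 6% |
| 0.3 | +3.5 to +4.2 | +2.3 to +2.7 | 7–8% |
| 0.5 | +5.0 to +7.6 | +3.9 to +4.8 | 12–15% |
| 0.7 | +5.1 to +11.7 | +5.7 to +7.4 | 19–29% |

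With failure at 35% in both arms, every difference is zero.

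**6. The interaction term.** Under the 80/60/40 gradient the odds ratio is 4.00/2.50 = 1.60 among failures and 0.778/0.667 = 1.17 among successes, a ratio of 1.37. With the group sizes in step 2, the standard error of the log ratio is about 0.49, so z = 0.316/0.49 = 0.64. About 10% of trials would find a nominally significant interaction, against 5% by chance.

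**7. A true benefit.** Add 10 points of BPD risk to any infant who fails, again under 80/60/40. Overall BPD becomes 51 + 0.20×10 = 53.0% on NIV-NAVA and 51 + 0.35×10 = 54.5% on NS-NIPPV. The benefit is real, yet the groups still show +8.6 (90.0% against 81.4%) and +3.8 points against NIV-NAVA.

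**The case against.** The best defence has four parts.

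- **Wording.** The passage on failure and reintubation names no model, estimand or causal claim. The subgroup-by-arm method is stated one paragraph earlier, and applying it here is plausible but inferred. This is a condensed article, so model detail may sit elsewhere. That stands as to detail. It does not remove the stated commitment to explore interactions that include arm and post-randomisation variables.
- **Exploratory status.** The endpoint section uses exploratory and associational language. That deals with power and multiplicity. It does not correct a contrast whose expected value is wrong, and a larger sample would not help.
- **Inputs.** The BPD gradients and correlations are assumed. Steps 3 to 6 are unadjusted, and a model with gestational age, sex, site and ventilation days should absorb part of the severity gradient. If some infants fail only on NIV-NAVA, the excess among failures falls from +8.6 to +4.3 points. All of this stands and limits the size, not the direction in these examples.
- **An unbiased comparison is already planned.** The as-randomised analysis of secondary outcomes would be available beside any subgroup result. This also stands.

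A reader might infer that the planned analyses are bound to show spurious differences, or to make NIV-NAVA look harmful on every 36-week outcome. The documents do not support that. The bias needs a true effect on failure or reintubation together with shared severity. The protocol's stated link is to BPD; it gives no gradient for the other outcomes.

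**Conclusion.** The concern holds in conditional form. The protocol plans exploratory arm contrasts or interactions within groups formed by variables that treatment is designed to change, and randomisation does not protect them. If NIV-NAVA lowers failure from 35% to 20%, and unmeasured severity drives both failure and BPD, a false excess of BPD on NIV-NAVA is expected in both groups: about +2 to +9 points under the assumed gradients, and up to about +12 at the strongest correlation tried. The bias is zero if failure rates are equal or there is no shared severity. A nominally significant false result would be uncommon at moderate correlations (about 6% to 15% at 0.2 to 0.5).

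It would go too far to conclude that the trial's primary or main 36-week findings are compromised. Those comparisons are made as randomised and are untouched. What is at risk is the guidance that these subgroup results are meant to give to future trials.

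**What to change.** In the section on additional analyses {20b}:

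- State that arm contrasts within failure or reintubation groups, and arm-by-failure or arm-by-reintubation interactions, will not be interpreted as treatment effects. Drop them, or tabulate them as descriptive and non-causal only.
- Estimate the association of extubation failure with BPD pooled over arms, adjusted for arm, gestational age, sex and ventilation days, and report it as an association. This serves the aim already given under Secondary study endpoints.
- If the route through failure is of interest for future trials, pre-specify a mediation or principal-stratum analysis, with its assumptions and a sensitivity analysis for unmeasured severity.

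The cost is wording and analysis code. No new data are needed, and the sample size and primary analysis do not change. The downside is that the within-failure-group arm contrasts are given up as inferential results.

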## Participant timeline {13}

### Duration of study participation

Figures 1 and 2 outline the timing of enrollment, trial interventions, and data collection. Subject participation will commence upon enrollment following informed consent in the trial, as early as 24 weeks PMA, and will continue until all secondary outcomes are ascertained by 36^6/7^ weeks PMA. Thus, the total duration of study participation will be up to 13 weeks for each study subject.

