### Plans to promote participant retention and complete follow-up {18b}

The study follow-up phase will commence after primary outcome ascertainment and continue until 36 weeks PMA, death, or hospital discharge/transfer (whichever is first). Only randomized patients will be followed (there will be no follow-up for patients in the run-in phase).

For subjects whose parents withdraw consent to participate in the study, the study team will request permission for ongoing collection and use of study-related measures and endpoints from the medical record*.*

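### If the weaning times are analysed as time-to-event outcomes, censoring at death overstates the proportion weaned alive and can mask an arm difference when deaths differ

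*Protocol article*

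**What the plan says.** All references are to the protocol article.

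- *Methods for additional analyses {20b}* deals with death in the later outcomes. It begins with a permissive sentence, "For non-mortal 36 weeks’ PMA/discharge secondary outcomes, death many be a censoring event" (the fifth word from the end of that clause, before the verb, is evidently meant as *may*). It goes on, "Rates will be summarized and compared within all infants and within survivors only", and ends with a firm rule: "Death will be coded as time of censoring in time-to-event outcomes".
- *Statistical methods for primary and secondary outcomes {20a}* lists model families by type of outcome, ending with "survival analysis (time based outcomes), as appropriate". It does not say which outcome goes to which family.
- *Secondary study endpoints* lists the postmenstrual age at which an infant last needed ventilation, positive pressure and oxygen. It also lists intubation with its timing, time to death, and a death/BPD composite. It labels the analyses of later respiratory outcomes exploratory and adds: "The DIVA trial is not powered to identify the impact of NIV-NAVA on all later respiratory outcomes".
- *Plans to promote participant retention {18b}* has follow-up "continue until 36 weeks PMA, death, or hospital discharge/transfer (whichever is first").

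The article names no cumulative-incidence or rank-based analysis for the timed outcomes.

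**The concern.** Ordinary censoring means that observation stops while the event could still happen. That is a fair description of an infant who is transferred, or who reaches 36 weeks still on support. It does not describe an infant who dies on the ventilator, for whom weaning is no longer possible. If that death is coded as censoring, the Kaplan-Meier estimator spreads the infant's remaining probability over those still at risk, as though the infant would have weaned at their rate. The curve then describes weaning in a population where nobody dies, and its medians and 36-week percentages should not be read as what happened to the randomised infants.

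At stake is the comparison of respiratory courses after extubation. *Methods for additional analyses {20b}* regards analyses of the 36-week outcomes as important for designing future trials. If more infants died on support in one arm, fewer would be weaned alive there, yet the censored curves could look the same.

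Two provisions come near the problem but do not solve it. The all-infants and survivors-only comparison concerns rates, and its survivors-only half conditions on a post-randomisation event. The death/BPD composite is binary. Neither changes a time-to-event curve.

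**Working it through.** **Figures in the plan.** The article gives no rate, effect or power for any time-to-event outcome, so there is no figure of its own to reproduce here. The sample size of 478 is for the five-day binary primary outcome and does not enter.

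**Inputs, all assumed.**
- Constant weekly weaning hazard *w* = 0.10, the same in both arms.
- Constant weekly hazard of death on support *d* = 0.01, 0.02 or 0.04.
- Horizon *T* = 10 weeks. *Duration of study participation* gives a maximum: "the total duration of study participation will be up to 13 weeks for each study subject".
- Weaning is treated as a single event, a simplification.

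**Formulas.**
- Kaplan-Meier with deaths censored: 1 − exp(−*wT*).
- Cumulative incidence of weaning alive: *w*/(*w*+*d*) × [1 − exp(−(*w*+*d*)*T*)].
- Deaths on support: *d*/(*w*+*d*) × [1 − exp(−(*w*+*d*)*T*)].
- Time at which half are weaned alive: −ln[1 − 0.5(*w*+*d*)/*w*]/(*w*+*d*).

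**Numbers.** Censoring gives 1 − exp(−1.0) = 63.2% whatever the mortality, with a median of ln 2/0.10 = 6.9 weeks. Cumulative incidence gives:
- *d* = 0.01: 0.10/0.11 × (1 − e^−1.1) = 60.6%
- *d* = 0.02: 0.10/0.12 × (1 − e^−1.2) = 58.2%
- *d* = 0.04: 0.10/0.14 × (1 − e^−1.4) = 53.8%

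| Death hazard | Die on support | Weaned, deaths censored | Weaned alive | Excess (points) | Half weaned alive by (weeks) |
|---|---|---|---|---|---|
| 0.01 | 6.1% | 63.2% | 60.6% | 2.6 | 7.3 |
| 0.02 | 11.6% | 63.2% | 58.2% | 5.0 | 7.6 |
| 0.04 | 21.5% | 63.2% | 53.8% | 9.4 | 8.6 |

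**Between arms.** If the arms had death hazards of 0.02 and 0.04, the censored curves would coincide at 63.2%, while the proportions weaned alive would differ by 58.2 − 53.8 = 4.4 points. If both arms had 0.02, both would be overstated by 5.0 points and no difference would be hidden.

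**Other assumed rates.** Here the death hazard was solved to give a chosen percentage of deaths by 10 weeks.
- *w* = 0.15, deaths 5% and 15%: 77.7% in both arms with censoring, against 74.8% and 68.9% weaned alive (excess 2.9 and 8.8 points).
- *w* = 0.25, deaths 10% and 20%: 91.8% in both arms, against 83.9% and 75.8% (excess 7.9 and 16.0 points).

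Across deaths of 5% to 20% and *w* from 0.15 to 0.25, the excess runs from about 3 to 16 points. At a given weaning hazard it is always larger where more infants die.

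**The case against.** **Censoring at death is a standard method.** It is how a cause-specific hazard is estimated, and that hazard is a legitimate basis for comparing arms. In the illustration the weaning hazards are equal, so a cause-specific hazard ratio of 1 is the right answer to its own question, and the 4.4-point gap comes wholly from mortality. This stands. What remains is that the hazard ratio does not give the proportion weaned alive, and Kaplan-Meier curves and medians drawn from the same coding give it wrongly.

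**The affected outcomes are inferred.** Ages at last support might go to linear regression instead, and then the censoring rule would not reach them. This also stands, and the point is conditional on it.

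**A reader might infer that censoring favours the arm with more deaths.** The documents and the arithmetic do not support that as a general claim. The illustration makes the arms look equal; it does not reverse them. A tilt appeared only in a simulation that added a shared frailty, under which sicker infants wean more slowly and die more often. With deaths of 5% and 15% and no treatment effect on weaning, the censored percentages were 82.1% and 83.3% (actual 79.3% and 74.0%), a weaning rate ratio of only 1.04. For a harmful event the direction changes. With an intubation-type hazard of 0.05 per week and the same death percentages, censoring gives 39.3% in both arms, against 38.2% and 35.8%, which overstates harm most where deaths are most frequent.

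**A reader might also infer that time to death itself would be censored at death.** That is a strained reading. The discussion of death opens by restricting itself to non-mortal outcomes, and time to death is listed as an endpoint of its own.

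**Deaths are visible elsewhere.** Time to death, the death/BPD composite and serious adverse event reporting would all show an imbalance. True, but they would not correct the weaning curve beside them.

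**The article is a condensation.** The analysis plan is not shown and the reference cited for the sentence was not available. The absence of a named competing-risk method is therefore no finding; the point rests on the rule that the article does state.

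**Conclusion.** The point holds in a limited form. If the ages at last ventilation, positive pressure and oxygen are analysed as time-to-event outcomes, as the text implies but does not state, then coding death on support as censoring makes Kaplan-Meier weaning probabilities too high and medians too early. With an assumed weaning hazard of 0.10 per week over 10 weeks and deaths of about 6% to 21%, the excess is about 3 to 9 points; faster weaning with similar deaths extends it to about 16. These sizes rest entirely on assumed constant hazards, because the article gives no rates.

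A difference between arms in infants weaned alive can be masked only if deaths on support differ by arm. The cause-specific hazard ratio remains valid as one summary. The outcomes are exploratory, and neither the primary analysis nor the 478 infants is affected. This is an inexpensive improvement to a secondary analysis, not a threat to the trial's main conclusion.

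**What to change.** Replace the censoring sentence in *Methods for additional analyses {20b}* with wording such as:

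> *For non-mortal time-to-event outcomes, death is a competing event: cumulative incidence by arm (Aalen-Johansen), with a between-arm comparison on that scale, is reported alongside the cause-specific hazard ratio; survivors-only comparisons are descriptive.*

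This would also settle the uneven wording in that section, where death may be a censoring event in one sentence and will be one in another. It would help to state in the same place which secondary outcomes are analysed as time-to-event.

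The cost is one sentence and modest programming. Dates of death and start and stop dates of each mode of support are already collected (Table 5). The downside is that two effect measures must be explained in the report. The change should be made before outcome data are compared by arm, so that the choice of summary cannot be seen as post hoc.
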